### Design (Fig. 1)

This study will be a prospective, multi-facility, single-blind, crossover, randomised controlled trial. Haemodialysis patients will be allocated randomly and equally to either an Early-sequence or Later-sequence group. For the Early-sequence group, patients will receive cannulation while not listening to sound (only wearing headphones) during the first (run-in) week (No-sound period), listen to music during the second week (music period), listen to no-sound during the third (washout) week (No-sound period), and listen to white noise during the fourth week (White noise period). For the Later-sequence group, the no-sound period commences in the first (run-in) week, white noise during the second week, no-sound during the third (washout) week, and music during the fourth week.

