### Sample size

We conducted a pilot two-arm randomised controlled trial at four facilities, whereby eight haemodialysis patients were assigned randomly into either of the two groups: Group 1 listened to Mozart, and Group 2 listened to the news on the radio. The primary outcome was cannulation pain evaluated via a VAS. A previous review suggested that patients who record a baseline VAS score of more than 30 mm might indicate at least moderate pain [65]. Moura and colleagues reported that 20% of the haemodialysis patients suffer from pain, indicated by a VAS pain score of more than 30 mm [4]. In our pilot study, the mean VAS results were 20.5 mm in Group 1 and 25.4 mm in Group 2. All VAS scores were normally distributed, and the standard deviation was 12.0 mm. Based on results of clinical trials of analgesic agents [66, 67] and a cost-benefit performance of music therapy, a difference of 4.9 mm was considered to be clinically significant and was used for the sample size design. From these results, we computed that 95 patients are needed to observe a treatment effect based on this effect size at a power of 80% with a two-sided significance level of 5%. Assuming participant attrition, we will recruit a total of 120 participants. As the proposed study is a crossover trial wherein the statistical power is assumed to be greater than that of a two-arm design, we believe that our study is adequately powered.

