### Analyses

#### Analysis of VAS pain scores during the cannulation

A set of outcome variables, which includes the VAS pain score as the primary outcome and the VAS anxiety score, STAI score, and S-AMY as the secondary outcomes, will be assessed during a single dialysis session. Each study period will last for a week including three dialyses. Patients will undergo two study periods; thus, each patient will be assessed for six sets of the outcome variables (three in the music period and other three in the white noise period).

A linear mixed model will be applied to compare the means of the three repeated outcome measures between the music and the white noise periods. For the outcome that accompanies the baseline measures, the mixed model will compare the mean of three repeated change scores between the two periods. Compound symmetry was used for variance-covariance to estimate dependency among the repeated measures. Two-sided significance level will be set at 0.05. The normality of the residuals will be confirmed via Q-Q plots, and the mathematical transformation of the outcome variable will be performed if necessary. The mixed-model approach was chosen on the basis of a Monte Carlo simulation study in order to compare the statistical power of three different analytical strategies, which include the following (see Additional file 2).
Paired *t* test to compare the two means of three pain scores between the two periods. (The unit of observation in the analysis is the within-patient mean score of the three scores; the analysis includes two mean scores per patient.)Linear mixed model to compare the two means of the three pain scores between the groups. (The unit of observation is the same as 1.)Linear mixed model to compare the six pain scores between the two periods. (The unit of observation is the pain scores; the analysis includes six observations per patient.)

The third approach was chosen because it appeared to be superior to other approaches, as it provides the largest statistical power to detect statistical significance while controlling for type I error. In addition, the direct inclusion of all six observations will allow us to control for time-dependent confounders, such as personnel effect from the operator who performs the cannulation.

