A few study limitations should be noted. First, participants cannot be made blind to their intervention allocation and some of the outcome measures. To address this issue, we will tell participants that both music and white noise are known to facilitate relaxation. Furthermore, all VAS assessments will be conducted without operator assistance. Therefore, all reports will be kept confidential. Second, this is a crossover randomised controlled trial and carry-over effects could occur. To minimise this possibility, we will implement a washout period (1 week) between the white noise and music periods. If carry-over effects emerge, we will use only data from the second week (HD5–7) for the analysis, as it is a randomised parallel-group design. The current sample size was computed on the basis of the single period data alone; thus, the estimated sample size would be sufficient for the period-specific analysis. Third, the proposed study will be somewhat protracted (no fewer than 4 weeks for each patient). Therefore, there is a risk of participant dropout, which could create a selection bias. We will try to alleviate dropout through monetary incentives for participation [85].

The proposed protocol will include a multi-facility, operator-blind, crossover randomised controlled trial to examine whether music therapy successfully reduces cannulation pain for dialysis patients. If predicted results manifest, we should have evidence that patients’ cannulation phobia and pain experiences can be reduced through a safe and cost-effective treatment strategy.

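### The carry-over rule lets the trial's own data choose the primary analysis, so the stated 5% error level is not secured, and the sample-size support for the fallback fails on the protocol's own inputs

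*Protocol article*

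**What the plan says.** The section on analysis of VAS pain scores names a linear mixed model comparing six pain scores per patient between the music and white noise periods, with compound symmetry. It states "Two-sided significance level will be set at 0.05". It justifies the model by a simulation of three analysis strategies, each applied as a fixed choice.

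The limitations paragraph of the Discussion then adds a contingency: "If carry-over effects emerge, we will use only data from the second week (HD5–7) for the analysis". It treats that analysis as a randomised parallel-group comparison. It says that the sample size was worked out from a single period and would therefore be enough for it.

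The Sample size section gives the inputs: "a difference of 4.9 mm was considered to be clinically significant" and "the standard deviation was 12.0 mm", with 80% power and a two-sided 5% level. From these, "we computed that 95 patients are needed to observe a treatment effect"; it does not say whether that is per group or in total. Then: "Assuming participant attrition, we will recruit a total of 120 participants". Allocation is equal (Design section), so 60 per sequence.

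**The concern.** The switch is a test-then-choose procedure. The usual carry-over contrast compares patient totals (both sound periods added) between sequences, and those totals contain the HD5–7 scores. If that contrast is large by chance, the HD5–7 contrast tends to be large too. The fallback would then be used mostly in trials where its own test is already shifted away from zero. In that case the procedure as a whole exceeds the stated 0.05 for the primary outcome, even though each component test holds it.

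The switch also gives up the within-patient comparison that the Discussion offers as the reason for a crossover. It rests on a statement of adequate sample size that can be checked from the protocol's own figures.

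**Working it through.** **1. The plan's own figure.** Inputs from the Sample size section: difference 4.9 mm, SD 12.0 mm, two-sided 5%, power 80%. For a two-group comparison of means:

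n per group = 2 × [12.0 × (1.960 + 0.842) / 4.9]² = 94.1, rounded up to 95.

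So 95 reproduces, but as the number **per group**, or 190 in total. One other reading comes close: a paired design whose SD of differences is 12 × √2 needs 96–97 patients in total. That is not the single-period calculation which the Discussion says was made.

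**2. Power of the HD5–7 fallback.** Power = Φ(4.9/SE − 1.96), with SE = SD × √(2/n) and n per group.

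| Patients | SD of analysed score | SE | Power |
|---|---|---|---|
| 60 per sequence | 12.0 | 2.19 | 61% |
| 95 in total (47.5 per sequence) | 12.0 | 2.46 | 51% |
| 95 per sequence | 12.0 | 1.74 | 80% |

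If 12.0 mm is instead a single-session SD and three sessions are averaged, the SD becomes 12.0 × √((1 + 2·ICC)/3). The protocol gives no ICC. With 60 per sequence, an assumed ICC of 0.5 gives SD 9.80 and power 78%; an ICC of 0.8 gives SD 11.17 and power 67%. Power passes 80% only at an ICC somewhat below 0.5.

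**3. Type I error with the switch.** Three inputs are assumptions because the protocol gives none of them: the carry-over test (between-sequence, on patient totals), its level a (5% or 10%), and the correlation ρ of a patient's two period means (0 to 1). There is no treatment or carry-over effect.

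- With equal variances, the within-patient contrast is independent of the totals contrast.
- The totals contrast Z_sum and the HD5–7 contrast Z₁ have correlation √((1 + ρ)/2), which is 0.71 at ρ = 0 and 0.94 at ρ = 0.75.
- Overall error = 0.05 × (1 − a) + P(|Z_sum| > z_a and |Z₁| > 1.96), from the bivariate normal.

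Example, a = 10%, ρ = 0.5: 0.05 × 0.90 + 0.037 = 0.082.

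| ρ | Error, a = 5% | Error, a = 10% | False-positive rate given a switch (5% / 10%) |
|---|---|---|---|
| 0 | 6.4% | 7.0% | 34% / 25% |
| 0.5 | 7.4% | 8.2% | 53% / 37% |
| 0.75 | 8.1% | 8.9% | 67% / 44% |
| 0.85 | 8.5% | 9.2% | 74% / 47% |
| 1 | 9.75% | 9.5% | 100% / 50% |

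A simulation with 60 per sequence, three sessions per period, compound symmetry and 50,000 trials per setting agreed. At a single-session ICC of 0.5 (ρ = 0.75) it gave 8.0% for a = 5% and 8.6% for a = 10%.

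**4. Other ways of judging carry-over.** VAS pain is also recorded in the run-in week (HD2–4) and the washout week (HD8–10), so two further tests are possible.

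- *Washout week compared between sequences.* Its correlation with Z₁ is ρ. The same formula gives 5.7–7.3% (a = 5%) and 6.0–8.1% (a = 10%) for ρ from 0.5 to 0.85.
- *Change from run-in to washout compared between sequences.* Under compound symmetry this is uncorrelated with both the HD5–7 contrast and the within-patient contrast. The error stays at 5.0%.

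**The case against.** The strongest reply is that the inflation is not a fixed property of this protocol. A reader might infer that the rule raises the error to some definite figure such as 7.5–9%. The document does not support that, because it names no carry-over test, no level and no correlation. Its no-sound weeks also allow a check that would cost nothing in type I error. This stands: the percentages hold only under the stated assumptions. It does not rescue the rule, because the harmless test is nowhere specified, and an undefined trigger leaves test and threshold open to choice after results are seen.

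A second reply is that the switch is a contingency in a limitations paragraph. With no carry-over, a 5–10% test would trigger it in only 5–10% of trials, and the mixed model by itself holds 5%. That is correct. The high false-positive rates given a switch apply only to that uncommon event; the overall error is the figure to judge by.

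Two further inferences go too far. One is that the carry-over test would have too little power to detect real carry-over; no calculation here addresses that. The other is that the crossover itself is underpowered; the shortfall shown concerns the HD5–7 fallback only.

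Nor can the rule be set aside as detail left to an analysis plan. It is stated outright and names the data to be used.

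**Conclusion.** The point holds in this form. The Discussion makes the choice of primary analysis depend on the trial's own data, without a defined trigger or any adjustment, so the stated two-sided 5% is not secured. If carry-over is tested on patient totals at 5–10%, the error exceeds 5% at every correlation from 0 to 1: about 6.4–9.75% overall, and about 7.4–9.2% for correlations of 0.5–0.85. That narrower band is plausible given the large individual differences the Discussion expects, but no figure in the document fixes it. Confidence is high that the rule is defective and moderate on the size.

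Separately, the statement that the sample size suffices for the period-specific analysis is wrong on the protocol's own inputs. Power is about 61% with all 120 patients and about 51% with 95 in total, taking 12.0 mm as the SD of the analysed score. Averaging three sessions would raise it, reaching 80% with 60 per sequence only if the within-patient correlation between sessions is somewhat below 0.5.

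**What to change.** - Delete the switching rule. Keep the mixed model on both sound periods as the only primary analysis, whatever the carry-over estimate. Type I error then returns to 5.0%.
- Report the carry-over (sequence) estimate with its confidence interval, descriptively.
- Report HD5–7 by sequence, adjusted for the HD2–4 mean, as a sensitivity analysis only.
- Remove the sentence on sufficiency for the period-specific analysis, or restate it with the power that 60 per sequence gives and the SD assumed.

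The cost is a few sentences, settled before unblinding; no data collection or patient procedure changes. The downside is that if real carry-over outlasts the one-week washout, the primary estimate keeps some bias. The HD5–7 sensitivity analysis is there to show it.

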### Study protocol

Figure 1 outlines the trial protocol and randomisation procedure. The intervention will be performed during each study period from the time of cannulation to the start of dialysis (thrice a week) (Table 1).

**Table 1 Tab1:** Summary of collected data at each time point according to SPIRIT 2013 guideline

TIME POINT	Enrolment HD1	1 week			1 week			1 week			1 week		
		HD2	HD3	HD4	HD5	HD6	HD7	HD8	HD9	HD10	HD11	HD12	HD13
ENROLMENT													
Eligibility screening	×												
Informed consent	×												
Allocation	×												
INTERVENTIONS													
Early-sequence													
No-sound		×	×	×				×	×	×			
Music					×	×	×						
White noise											×	×	×
Later-sequence													
No-sound		×	×	×				×	×	×			
Music											×	×	×
White noise					×	×	×						
ASSESSMENTS													
Baseline information	×												
VAS pain score		×	×	×	×	×	×	×	×	×	×	×	×
VAS anxiety score		×	×	×	×	×	×	×	×	×	×	×	×
STAI Y-1				×			×			×			×
STAI Y-2	×												
BP and HR		×	×	×	×	×	×	×	×	×	×	×	×
S-AMY				×			×			×			×
Conditional information		×	×	×	×	×	×	×	×	×	×	×	×
Adverse events		×	×	×	×	×	×	×	×	×	×	×	×

*Abbreviations*: *BP* blood pressure, *HD* haemodialysis, *HR* heart rate, *S-AMY* salivary amylase activity, *SPIRIT* Standard Protocol Items: Recommendations for Interventional Trials, *STAI* State-Trait Anxiety Inventory, *VAS* Visual Analogue Scale

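### If carry-over is declared, the HD5–7 fallback compares different patients without adjusting for the pre-sound HD2–4 pain scores the trial already collects

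*Protocol article*

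**What the plan says.** Under Design, both sequences spend week 1 wearing headphones with no sound, before the first sound week. Table 1 (Study protocol) marks the "VAS pain score" at every session from HD2 to HD13, so each patient has three run-in scores.

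The primary analysis is a linear mixed model in which "the analysis includes six observations per patient": three under music and three under white noise. Its covariance is stated: "Compound symmetry was used for variance-covariance to estimate dependency among the repeated measures".

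The limitations paragraph of the Discussion gives the fallback. If carry-over emerges, "we will use only data from the second week (HD5–7) for the analysis", and the comparison becomes a randomised parallel-group one. The same paragraph says the sample size is enough for that analysis, because it was computed from single-period data.

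The no-sound weeks are otherwise used in a secondary comparison with each sound (Discussion). The change-score sentence under Analyses covers outcomes that have a baseline measure but names none. VAS pain has no pre-cannulation measure within a session, so that sentence does not clearly reach it.

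**The concern.** The Discussion justifies the crossover by warning that, in a parallel-group trial, differences between individuals could hide the treatment effect. The fallback brings back exactly that design and takes no step against the problem. The run-in scores are the natural remedy. They are the same outcome on the same scale, they come before any sound, they are collected identically in both sequences, and patients are not told their sequence in advance.

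At stake is the trial's main conclusion if carry-over is declared. That conclusion would then rest on one week of between-patient data, with avoidable noise in the error term.

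**Working it through.** **Inputs.** From Sample size: difference 4.9 mm, SD 12.0 mm, two-sided 5%, 80% power, 95 patients needed, 120 recruited. From Design: equal allocation. Not given: the correlation ρ between two sessions of one patient, and whether 12.0 mm is the SD of a single session or of the score to be analysed. Both are treated as assumptions below.

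**The plan's own figure.** For two independent groups, n per group = 2(1.960 + 0.842)² × 12.0² / 4.9² = 94.1, rounded up to 95. The stated 95 is therefore the size of one group in a parallel comparison, or 190 in total. As a total, 95 fits only a paired comparison with zero within-patient correlation. In the fallback, with one unadjusted score of SD 12, power is 50% at 95 in total and 60% at 120 (noncentral t).

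**Formulas for the fallback, equal correlation ρ.**
- Variance of a patient's mean of three scores: 144(1 + 2ρ)/3.
- Correlation of the HD2–4 mean with the HD5–7 mean: R = 3ρ/(1 + 2ρ).
- Variance after adjusting for the run-in mean: the first line × (1 − R²).

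With complete data and compound symmetry, a mixed model on the three HD5–7 scores gives the same comparison as these means.

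*Example, ρ = 0.5, 48 versus 47 patients.* SD of the mean = 12√(2/3) = 9.80 mm. R = 1.5/2 = 0.75 and 1 − R² = 0.4375, so the adjusted SD is 6.48 mm. The standard error falls from 9.80 × √(1/48 + 1/47) = 2.01 to 1.33 mm. The ratio 4.9/SE rises from 2.44 to 3.69.

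**Reading A: 12 mm is the SD of one session; the mean of three is analysed.**

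| ρ | R | 1 − R² | Power, N = 95, without → with | Power, N = 120, without → with |
|---|---|---|---|---|
| 0.3 | 0.56 | 0.68 | 77% → 90% | 86% → 96% |
| 0.5 | 0.75 | 0.44 | 67% → 95% | 78% → 98% |
| 0.7 | 0.88 | 0.23 | 60% → 99.5% | 70% → 99.9% |

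At low correlation the gain is small: with ρ = 0.1 and N = 95 it is 88% → 90%.

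**Reading B: 12 mm is the SD of the analysed score.** Here R is assumed directly.

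| R | 1 − R² | Power, N = 95, without → with | Power, N = 120, without → with |
|---|---|---|---|
| 0.3 | 0.91 | 50% → 54% | 60% → 64% |
| 0.5 | 0.75 | 50% → 62% | 60% → 73% |
| 0.7 | 0.51 | 50% → 79% | 60% → 87% |

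**If correlation decays between weeks (reading A).** Let a part w of ρ shrink by a factor a from one week to the next. Then R = (ρ − w + wa)/((1 + 2ρ)/3).
- ρ = 0.5, w = 0.5, a = 0.5: R = 0.25/0.667 = 0.375. The variance factor is 0.86 instead of 0.44.
- ρ = 0.7, w = 0.4, a = 0.7: R = 0.58/0.80 = 0.725. The factor is 0.47 instead of 0.23.

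Across the scenarios tried, the factor ran from 0.47 to 0.86: still a gain, but a smaller one.

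**Primary crossover model.** Adding HD2–4 to the six-score model with period effects leaves the variance of the treatment effect unchanged (ratio 1.000) under compound symmetry with complete data. A patient's constant level already cancels from music minus white noise. With 10–20% dropout before week 3 the variance falls by 1–5%, and with between-week decay by about 2–8%. Primary power at N = 95 under reading A is already about 0.95 or more in all these cases.

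**The case against.** The strongest objection is that covariates of a contingent analysis are normally settled in the SAP, which is not at hand. The restriction to HD5–7 may also be meant only to exclude the fourth-week outcomes, not a pre-treatment covariate. That reading is possible. But the sentence is a positive restriction on the data to be used, and taken literally it rules the run-in scores out. It sits beside the claim that the sample size is enough for this analysis. The point is therefore a concrete improvement to a stated method, not a complaint that detail is missing.

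A second objection is that 95 patients and equal correlation flatter the gain. The fallback needs only week-2 scores, so the number analysed may lie nearer 120, and decay between weeks weakens the covariate. Both stand, which is why the results are shown at both sizes, under both readings of the SD, and with decay.

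A reader might go further and infer three things that the documents do not support:
- *That the primary model also loses material precision.* Under its own compound symmetry the loss is nil with complete data, and a few percent of variance otherwise.
- *That the run-in data are wasted.* They serve the planned secondary comparison with no-sound.
- *That the unadjusted fallback is biased by the missing covariate.* First-period groups are randomised, so the loss here is one of precision.

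**Conclusion.** The point holds for the carry-over fallback only. As worded, that analysis sets aside a valid pre-treatment measure of its own outcome and leaves individual differences in the error term. At the 95 patients the plan says are needed, the gain in power is 13 to about 40 percentage points under reading A with ρ from 0.3 to 0.7, and 4 to 29 points under reading B with R from 0.3 to 0.7. It shrinks at lower correlation or with decay between weeks. These sizes rest on correlations the protocol does not give; the direction of the gain does not depend on the exact value.

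The covariate does not make the adequacy claim for the fallback safe. Under reading B at 95 patients, power stays just below 80% even with R = 0.7. Nor does it address the choice to switch analysis on the basis of observed carry-over. It matters only if carry-over is declared, but it should be fixed beforehand, because adding a covariate after seeing carry-over would be data-driven.

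**What to change.** In the limitations paragraph of the Discussion, or wherever the fallback is formally specified, state that the HD5–7 analysis is a linear mixed model with sound condition and each patient's mean HD2–4 VAS pain score as a covariate. Add that the week-3 scores (HD8–10) are not used as a covariate because they follow the first sound week. Leave the primary crossover model as it is.

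The cost is one sentence and one degree of freedom, with no new data and no extra patients. The change should be recorded before outcome data are examined by sequence; since no interim analysis is planned, nothing in the protocol stands in the way of that.

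### The statement that the sample size suffices for the HD5–7 parallel-group fallback is not supported: the inputs give 95 patients per group, but 95 and 120 are used as totals

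*Protocol article*

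**What the plan says.** The Sample size section starts from a parallel design: "We conducted a pilot two-arm randomised controlled trial at four facilities". It reports that "the mean VAS results were 20.5 mm in Group 1 and 25.4 mm in Group 2", and that "All VAS scores were normally distributed, and the standard deviation was 12.0 mm". From this, "a difference of 4.9 mm was considered to be clinically significant and was used for the sample size design". The result is that "we computed that 95 patients are needed to observe a treatment effect based on this effect size at a power of 80" per cent, with a two-sided 5% level, and then "Assuming participant attrition, we will recruit a total of 120 participants". The words per group do not appear. The gain from the crossover is mentioned only as an unquantified extra.

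The Design section allocates patients equally to the two sequences, so 120 patients means 60 per sequence.

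The limitations part of the Discussion sets out a fallback. If carry-over effects appear, only HD5–7 will be used, as a randomised parallel-group comparison. It says the sample size was calculated from single-period data alone and concludes: "thus, the estimated sample size would be sufficient for the period-specific analysis".

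**The concern.** A two-group calculation normally yields a number per group. If 95 is such a number, a trial of 120 in total falls well short of what a parallel-group analysis needs, and the Discussion gives an assurance that its own calculation does not provide.

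The fallback would replace the crossover comparison as the basis for the trial's conclusion. A non-significant result would then carry a stated claim of adequate power that has not been established. The article itself argues, when it justifies the crossover, that differences between individuals could mask the treatment effect in a parallel-group trial. The fallback is exposed to exactly that problem.

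**Working it through.** **Inputs.** From Sample size: difference 4.9 mm, SD 12.0 mm, two-sided 5%, power 80%, 95 patients, 120 recruited. From Design: equal allocation. From the Discussion: the fallback uses HD5–7, which is three sessions. Not given: whether 12.0 mm is the SD of one session or of a mean of sessions, and the within-patient correlation ρ between sessions. Both are treated as assumptions below.

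**Step 1: reproduce 95.** For two independent groups, n per group = 2 × (1.960 + 0.842)² × (12.0/4.9)² = 94.1, which rounds up to 95 (95.1 by the t test). The total is 2 × 95 = 190. As a two-group result, 95 is therefore a per-group number.

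**Step 2: can 95 be a total?**
- Two groups, one-sided 5%: 75 per group, 150 in total. No match.
- Paired, SD of the difference 12.0 mm: about 48 patients (49 by t). No match.
- Paired with zero within-patient correlation, SD of the difference 12.0 × √2: about 95 (96 by t). This matches, but it is a crossover calculation and does not support a parallel-group comparison, in which 95 patients means 47.5 per group.

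**Step 3: fallback power if 12.0 mm is the SD of the analysed weekly mean.** Two-sample t test, standardised difference 4.9/12.0 = 0.408:
- 120 patients (60 per group): power 60.2%; difference detectable with 80% power 6.2 mm.
- 95 evaluable (47.5 per group): power 50.4%; detectable difference 7.0 mm.

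**Step 4: fallback power if 12.0 mm is a single-session SD and three sessions are averaged.** SD of the mean = 12.0 × √((1 + 2ρ)/3).

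| Assumed ρ | SD of mean (mm) | Power, 120 | Power, 95 |
|---|---|---|---|
| 0.3 | 8.76 | 86% | 77% |
| 0.5 | 9.80 | 78% | 67% |
| 0.8 | 11.17 | 66% | 56% |

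By the normal approximation, 80% power needs ρ of about 0.46 or less with 120 patients, and about 0.26 or less with 95.

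**Step 5: effect of adjusting for the run-in week.** Table 1 shows pain scores at HD2–4, all without sound. With equal correlation between all sessions, the correlation between two three-session means is r = 3ρ/(1 + 2ρ): 0.56 at ρ = 0.3 and 0.75 at ρ = 0.5. The adjusted SD is the SD of the mean × √(1 − r²).
- Single-session reading: at ρ = 0.3 the adjusted SD is 8.76 × √(1 − 0.56²) ≈ 7.25 mm, and power is about 96% with 120 and 90% with 95. It is higher for ρ up to 0.8.
- Weekly-mean reading: at ρ = 0.3 the adjusted SD is 12.0 × √(1 − 0.56²) ≈ 9.92 mm, and power is about 77% with 120 and 66% with 95. At ρ = 0.5 it is about 92% and 85%.

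**The case against.** The best defence is that the fallback uses three sessions per patient and the planned mixed model takes every session's score. If 12.0 mm is a single-session SD, averaging reduces it, and with all 120 patients a correlation of about 0.46 or less gives 80% power. The fallback also falls in the second of four weeks, so fewer patients may be lost by then than over the whole trial, and the number available could lie between 95 and 120. This stands as far as it goes. A reader might infer that the fallback's power simply is 60%, or 50% after attrition, but the article does not say which SD it reports, so those figures are one case in a range. The defence does not rescue the sentence, however. The article does not argue from averaging and gives no correlation. It relies on the single-period calculation, and that calculation asks for 190 patients.

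A second objection concerns weight. The sentence is in the limitations, it applies only if carry-over appears after a one-week washout, and the main analysis does not depend on it. That also stands, and it limits how serious the point is.

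A reader might go further and infer that the whole trial is underpowered. The document does not support that. A total of 95 matches a paired comparison with zero within-patient correlation, and any positive correlation raises the crossover's power.

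**Conclusion.** The sufficiency statement does not follow from the calculation it cites, because a per-group number has been carried forward as a total. On the article's figures the fallback has about 60% power with 120 patients and about 50% with 95 evaluable if 12.0 mm describes the weekly mean. It has more if 12.0 mm describes one session, by an amount that depends on an unreported correlation. With the 95 evaluable patients planned for, unadjusted power stays below 80% unless 12.0 mm is a single-session SD and that correlation is about 0.26 or less. The arithmetic is certain; the exact power is not. The point should be corrected, but it concerns a contingent analysis and leaves the primary crossover comparison untouched.

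**What to change.** 1. In Sample size, state that 95 is the per-group figure for a two-arm comparison (190 in total), and say whether 12.0 mm is the SD of one session or of a mean of sessions.
2. In the Discussion, replace the sufficiency sentence with a statement that the HD5–7 comparison is not shown to have 80% power. Give the range: about 60% (120 patients) and 50% (95) if 12.0 mm is the SD of the weekly mean; from 86%/77% at correlation 0.3 to 66%/56% at 0.8 if it is a single-session SD.
3. If the HD5–7 comparison is kept, adjust it for the mean no-sound pain score at HD2–4. This is optional for correcting the error, but it raises power under either reading. Any adjusted figure must carry its condition: at least 95% (120) and 90% (95) for correlations of 0.3 to 0.8 holds only if 12.0 mm is a single-session SD with equal correlation across sessions. Under the weekly-mean reading it is about 77%/66% at 0.3 and 92%/85% at 0.5.

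The cost is wording and a less favourable stated figure. The covariate is already collected, and no patients or visits are added.
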